### Validation and Updating

We will use bootstrapping techniques to internally explore the need to correct for optimism in regression coefficients and performance measures of the dynamic risk prediction models. The dynamic risk prediction models, which will be developed in the oldest cohort (PIAMA), will be externally validated in the youngest cohort (Generation R). Validation is essential in order to determine the ability of a model to reliably predict the outcome in other populations and settings. If necessary, the models will be updated based on the validation results in both cohorts. Thus, we will study whether the models either remain stable or improve by removing or adding predictors that are available in the validation data. Finally, the model will be fit to the combined PIAMA and Generation R data, with the goal of achieving optimal precision of the estimated coefficients.

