**Methods:**

Data will be obtained from the Generation R (n=7893) and Prevention and Incidence of Asthma and Mite Allergy (PIAMA; n=3963) cohorts, two Dutch prenatally recruited cohorts. We will select candidate predictors that can be assessed during the first visit and/or during subsequent visits to the CHC center or pediatrician, including sex; parental age, education level, and BMI; smoking exposure; ethnicity; birth weight; gestational age; breastfeeding versus formula feeding; and growth data through the age of 6 years. We will design dynamic prediction models that can be updated with new information obtained during subsequent CHC visits, allowing each measurement to be added to the model. Performance of the model will be assessed in terms of discrimination and calibration. Finally, the model will be validated both internally and externally using the combined cohort data and then converted into a computer-assisted tool called *Pro***C**OR (Prediction Of Child CardiOmetabolic Risk).

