### Development of the Prediction Models

Dynamic risk prediction models will be developed in both cohorts. Missing values will be taken into account using advanced imputation techniques [36].

To design the dynamic risk prediction models, we will choose a statistical technique that can account for clustering of the data due to the collection of repeated measurements over time within children. This approach makes it possible to introduce repeatedly assessed risk factor information for children between birth and the age of 6 years into the model. For comparison purposes, the initial model (created at birth) will be updated with new information obtained at each visit, including the age of the child [37].

The statistical technique used in this study will be determined based on a comparison between existing simple and advanced statistical methods in order to handle repeatedly measured independent variables and a non-time-varying outcome variable in a prediction model, as described by Chen et al [38] and Tu et al [39]. We will compare the applicability of these methods for the development of prediction models for use by epidemiologists and clinical practitioners, and we will test the predictive quality of these models.

Backward selection will determine the final risk prediction models. The initial regression model, including all potential predictors, will be fitted in the dataset. To ensure sufficient power during the modeling process, we will optimize the balance between the number of variables and outcome “events” in the models [40].

Next, variables that have weak associations will be omitted from the model. We will use the Akaike information criterion (AIC) as a stopping rule to determine which variables should be removed from the model. For a single predictor, AIC equates to selection at *P*=.157 [40]. This relatively high *P* value results in the inclusion of weaker predictors in the model at the cost of potentially selecting a nuisance variable. Such a model usually performs well in new subjects [40].

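### The abstract presents the ProCOR model as externally validated, but the external test applies to the PIAMA model and not to the pooled model that goes into the tool

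*Protocol article*

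**What the plan says.** The protocol article describes development and validation in three places.

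- **Abstract, Methods:** "the model will be validated both internally and externally using the combined cohort data and then converted into a computer-assisted tool".
- **Methods, Development of the Prediction Models:** "Dynamic risk prediction models will be developed in both cohorts".
- **Methods, Validation and Updating:** the models are "developed in the oldest cohort (PIAMA), will be externally validated in the youngest cohort (Generation R"). Next, "If necessary, the models will be updated based on the validation results in both cohorts", and in doing so "we will study whether the models either remain stable or improve by removing or adding predictors that are available in the validation data". The last step carries no condition: "Finally, the model will be fit to the combined PIAMA and Generation R data", for the sake of precision of the coefficients.

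Validation and Updating also plans a bootstrap to explore whether coefficients and performance measures need correction for optimism. It does not say to which of the successive models this applies. Development and Pilot Testing of the Prediction Tools then turns the developed models into the tools. It has experts set action cutoffs in a Delphi study that weighs sensitivity, specificity and predictive values, and it pilots feasibility in three centers.

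**The concern.** Data used to fit a model cannot serve as external data for that same model. Once Generation R has been pooled into the final fit, and possibly used before that to change the predictor set, it is development data. A reader of the abstract would nevertheless take the tool's own model to be externally validated.

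Updating is a realistic prospect. Design and Setting describes PIAMA as mainly Caucasian, born 1996-1997, from urban and rural areas. It describes Generation R as a multiethnic Rotterdam cohort (56% Caucasian) whose mothers lived there in 2002-2006. Ethnicity is a candidate predictor, so its effects would be learned largely from Generation R, with no further cohort to test them in.

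At stake is which performance figures are attached to the tool and shown to those who set the cutoffs. The pilot lists reach, acceptability, compliance, referrals and time spent. It lists no adolescent outcomes, so it could not reveal miscalibration later.

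**Working it through.** **Tracing the data.** The main check concerns the order of steps.

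| Step (Validation and Updating) | Data used | Independent data left |
|---|---|---|
| Develop | PIAMA, n = 3963 | Generation R |
| External validation | Generation R, n = 7893 | none for any later model |
| Update, if necessary | validation results in both cohorts | none |
| Final fit, always | both cohorts | none |

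Children available to the final fit: 3963 + 7893 = 11,856, which is everyone in the two cohorts. Remaining for external validation of that model: 11,856 − 11,856 = 0. Fewer children will have outcome data (61% of the 7893 took part in Generation R follow-up, about 4815, and only subgroups of PIAMA were medically examined), but that does not free a cohort. The article does not state outright that the pooled model enters the tool. The order of the sections, and the word with which the pooled fit is introduced, leave no other natural reading.

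**Size, first illustration.** The article gives no event counts for the outcomes, so every setting here is an assumption: 25 independent normal candidates, 8 with real effects (log odds ratios 0.5 to 0.1 per SD); backward elimination while the Wald chi-square is below 2; 60 runs per row; new children from the same population. The AIC rule reproduces the article's figure: P(chi-square, 1 df, > 2) = 0.1573, stated as .157. Cells show AUC / calibration slope.

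| First + second cohort; prevalence | Pooled events | First-cohort model in second cohort | Pooled model in second cohort (own data) | Pooled model in new children |
|---|---|---|---|---|
| 1000 + 1500; about 15% | 366 | 0.689 / 0.786 | 0.720 / 1.001 | 0.704 / 0.915 |
| 3000 + 4800; about 15% | 1132 | 0.704 / 0.888 | 0.715 / 0.986 | 0.710 / 0.962 |
| 1000 + 1500; about 6% | 147 | 0.670 / 0.614 | 0.735 / 0.993 | 0.697 / 0.811 |
| 3000 + 4800; about 6% | 444 | 0.701 / 0.842 | 0.722 / 0.995 | 0.711 / 0.941 |

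Own data minus new children, AUC: 0.720 − 0.704 = 0.016; 0.715 − 0.710 = 0.005; 0.735 − 0.697 = 0.038; 0.722 − 0.711 = 0.011. In every row the single-cohort external result is too pessimistic for the pooled model and the own-data result too favourable. Neither figure describes the tool.

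**Size, second illustration.** This used 42 candidates with 8 weak effects and a 6.2% prevalence. That figure is borrowed from the Introduction, where it is the frequency of low HDL-C in normal weight children. Pooled at 3963 + 4815 = 8778 children, events are 0.062 × 8778 = 544. AUC was 0.682 apparent and 0.671 in new data, a gap of 0.011, with a new-data slope of 0.93.

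Both illustrations draw all children from one population, so differences between the cohorts are not included. The first re-selects predictors in the pooled data, which the plan would do only if updating is judged necessary.

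**The case against.** The strongest reply is that the sequence is standard: develop, validate elsewhere, update if required, refit on everything. The Introduction gives the same order, so testing the PIAMA model before any updating is already planned. The abstract's phrase may be shorthand for using the two cohorts together, and the statement that models are developed in both cohorts can be squared with a final fit to both. Most of this stands. It does not rescue the abstract, which attributes external validation to the model that is then converted.

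A reader might infer four stronger points that the document does not support:

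- That the pooled refit is itself an error. It is accepted practice and improves precision.
- That predictors will certainly be re-selected in Generation R. That step is conditional. The pooled refit is not, and it is enough on its own to leave no external data.
- That the bootstrap excludes the updating and the pooled fit. The article does not limit it to PIAMA, and which steps each bootstrap sample repeats is detail that a condensed article may leave to the full plan.
- That the tool's figures must come either from another model or from uncorrected own-data performance. Bootstrap-corrected figures are a third possibility that the article itself raises, and it does not say which figures the Delphi experts will see.

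It is also fair that cross-cohort testing in both directions still tests two single-cohort models. It supports the modelling procedure, not the pooled coefficients.

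**Conclusion.** The point holds in this form: the external validation belongs to the PIAMA model, the model placed in the tool has no external data, and the abstract says otherwise. This follows from the text and does not depend on any simulation.

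The numerical consequence is probably small for outcomes with many events: AUC gaps of 0.005 to 0.011 and new-data slopes of 0.93 to 0.96 at 444 or more pooled events. It is larger with few: a gap of 0.038 and a slope of 0.81 at 147 events. The blood pressure and lipid outcomes may lie nearer the second case, since only subgroups of PIAMA were examined. These sizes rest on assumed predictors, effects and prevalences. This is a correctable mismatch between claim and design that limits what may be concluded about the tool. It is not a flaw that invalidates the modelling plan, and it gives no ground for demanding compulsory shrinkage or a cohort-specific intercept.

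**What to change.** 1. Reword the abstract so that external validation refers to the test across cohorts. For example: the model developed in PIAMA is validated internally and, in Generation R, externally; a final model is then fitted to both cohorts and its performance reported after correction for optimism.
2. Reconcile Development of the Prediction Models with Validation and Updating on which cohort is used for development at which stage.
3. Report the PIAMA model in Generation R before any updating, as the stated order already implies. Add the reverse test (develop in Generation R, validate in PIAMA) with the same procedure, and label the pair as internal-external cross-validation of the procedure.
4. Keep the pooled fit. Report its bootstrap optimism-corrected AUC and calibration slope, with predictor selection and any updating repeated in each bootstrap sample. The updating decision therefore has to be written down as a rule that can be repeated.
5. Base the cutoffs on those corrected figures.

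The cost is computing time, some rewording and slightly less favourable reported performance. No new data are needed. An external test of the pooled model itself would need a third dataset, and until one exists the tool should be described accordingly.

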### Development and Pilot Testing of the Prediction Tools

After the models have been developed, they will be converted into computer-assisted tools (the *Pro*
**C**OR tools). These tools will be easily applicable in CHC, providing for repeated risk assessments, thereby aiding CHC professionals in their decision to give advice, offer extra follow-up consults, and/or refer children and their parents for preventive intervention or further diagnostics. By consulting with experts in a Delphi study, we will determine which cutoff values will be used for these actions, with the aim of achieving the optimal balance between sensitivity, specificity, positive and negative predictive values, and the perceived diagnostic and therapeutic burden for the parents and their children. Finally, the feasibility of the implementation will be assessed in a pilot study to be conducted in three CHC centers within the Netherlands. In this pilot, we will study the reach, frequency, and percentage of children with a predicted high risk of overweight and/or poor cardiometabolic outcome, acceptability of risk communication and risk assessments, satisfaction, the potential for stigmatization, protocol compliance, advice and referrals, maintenance, and time spent. For this purpose, questionnaires will be developed both for parents and for CHC professionals. Approval will be requested from the MEC before the start of the pilot study.

## Results

This is an ongoing research project, and the first results are expected in 2016. The study began in December 2013 and is funded by the Health Research and Development Council of the Netherlands (ZonMw Grant no. 200500006).

## Discussion

Our study will provide an individualized approach for primary prevention of overweight and poor cardiometabolic outcome by combining risk estimates with the existing general approach. This individualized, targeted approach will bridge an existing gap in the primary prevention of overweight and related adverse cardiometabolic outcomes. This is likely both important and relevant, given that the effects of secondary prevention of overweight and obesity have been disappointing—even among younger children—particularly over the long run [44]. Moreover, the success of universal primary prevention has been less pronounced in groups from lower socioeconomic backgrounds [22,24]. Importantly, the *Pro*
**C**OR tools will also enable the identification of children who already have high blood pressure and an abnormal lipid profile, thereby offering these children additional diagnostics and treatment options by their pediatrician; this is particularly relevant, as these adverse cardiometabolic outcomes tend to persist into adolescence and even adulthood, and are usually asymptomatic [10-12].

The success of the *Pro*
**C**OR tools when applied in early childhood will be reflected in the possibility to refer children with increased risk to a primary preventive program. Although such primary preventive interventions are relatively scarce, and although the majority of efforts have focused on developing secondary preventive interventions, several studies have demonstrated the potential benefit of applying primary preventive interventions in this extremely young age group [45-47]. In addition, primary preventive interventions aimed at the most susceptible individuals are often more effective than interventions that target the entire population [48]. Therefore, participating JOGG cities in the Netherlands have opted to implement interventions that are similar to Mini-MEND, a program aimed at children and families with increased risk at the age of 2-4 (or 5) years; this program is currently being evaluated in Australia and the United States [49-51]. Mini-MEND is the younger-age equivalent of MEND (Mind, Exercise, Nutrition, Do It!), a family-based intervention that was designed for older children and was found to be cost-effective in a randomized controlled trial [52].

The *Pro*
**C**OR tools can also be linked to Web-based content, including educational materials, advice, and/or referrals to evidence-based intervention programs, thus stimulating a healthy lifestyle and/or health care–seeking behavior. Finally, the risk estimates generated by the *Pro*
**C**OR tools can also be used to study the effectiveness of interventions, as a risk assessment of future overweight and related cardiometabolic outcomes is likely to be more predictive than the currently used definition of overweight using the cutoffs established by the IOTF [53].

Other methods have been developed to identify children who are at high risk for becoming overweight and/or developing adverse cardiometabolic outcome; such methods include the use of a single risk factor, combining risk factors, and developing risk models, risk algorithms, and risk charts. For example, in both Sweden and the United States, risk charts have been developed to predict adult overweight based on a single BMI measurement during childhood [54,55]. Another study performed in the United States reported crude risk estimates of being overweight by the age of 12 years based on one, two, or three BMI values measured between 2 and 4½ years of age [56]. In the United Kingdom, an overweight risk algorithm was developed to identify at-risk children at age 3 years based on predictors that were assessed in the first year of life [57]. To date, however, most risk models have not been dynamic and barely took into account individual BMI development. Moreover, extremely high-performance prediction models are required before acceptable large-scale implementation is possible in practice.

A strength of our study is that we will include additional candidate predictors, thereby helping optimize the performance—and hence the cost-effectiveness—of these models. Moreover, performing repeat risk assessments enables clinicians to both adapt to and individualize the strategies for each child based on new findings. This approach may contribute to the realization of more tailor-made primary prevention programs, with the aim of reversing the high risk of overweight and adverse cardiometabolic outcome in preadolescence.

One potential limitation of our study is that the outcomes of the prediction models were examined in early adolescence; moreover, the cohort data do not currently offer the opportunity to study these outcomes at adulthood. However, the timing of puberty is associated with adult obesity and poor cardiometabolic outcome [58]. On the other hand, the correlation between BMI SDS at age 10 years and BMI SDS at young adulthood is high (>0.7), suggesting that preventing high BMI SDS by the age of 10 years is relevant in terms of health outcome at adulthood [17]. In future studies, we will expand the prediction models with health outcomes at later ages.

By providing longitudinal guidance to children, the Dutch CHC is highly specialized with respect to the growth and development of children, suggesting that performing dynamic risk assessments is a very feasible approach in this setting. Therefore, the Dutch CHC is ideally positioned to help improve resource allocation by identifying high-risk children and excluding children with relatively low risk.

Finally, the tools that emerge from this study will be made available via the Internet, provided that stakeholders—including parents and/or their representatives—voice the need for Web-based access to the tools.

A potential disadvantage associated with applying the *Pro*
**C**OR tools is that it may cause harm due to stigmatization and parental and/or individual concerns. Therefore, we will investigate the effects of risk communication on possible unwanted side effects in the pilot study. At the same time, we must bear in mind that any potential harm due to the application of current cutoff points for overweight and/or obesity are currently unknown; moreover, the effectiveness of interventions that are based on risk assessments can only be studied after the prediction tools have been developed. Therefore, assuming that prediction tools with high sensitivity, specificity, and negative and positive predictive values can be developed, the next logical step would be to perform a randomized controlled trial designed to evaluate the effects of the prediction tools in combination with primary preventive intervention programs.

## Appendix

Multimedia Appendix 1 Review 1.

Multimedia Appendix 2 Review 2.

Multimedia Appendix 3 Review 3.

## Abbreviations

AIC: Akaike information criterion
BMI: body mass index
BMI SDS: BMI standard deviation scores
CHC: Child Health Care
FFQ: food frequency questionnaire
HDL-C: high-density lipoprotein cholesterol
IOTF: International Obesity TaskForce
JOGG: Jongeren op Gezond Gewicht (in English: Youth on Healthy Weight)
MEC: medical ethics committee
MEND: Mind, Exercise, Nutrition, Do It!
PIAMA: Prevention and Incidence of Asthma and Mite Allergy
ProCOR: PRediction Of Child CardiOmetabolic Risk
